### 11.3.3 Subgroup analysis

The following four subgroup analyses will be performed:

- 1) Participants: aged 20- to 64-years-old vs 65- to 80-years-old;
- 2) OAB severity: moderate (OABSS: 6 to 11 points) vs severe (OABSS: 12 to 15 points);
- 3) Pharmacotherapy: naïve vs past vs under treatment;
- 4) Incontinence: no (OABSS Q4 = 0 point) vs yes (OABSS Q4 = 1 to 5 point);
- 5) HADS Anxiety score: normal (0 to 7 points) vs borderline or abnormal (8 to 21 points)
- 6) HADS Depression score: normal (0 to 7 points) vs borderline or abnormal (8 to 21 points).

When possible and/or necessary,

- 7) Intervention type: face-to-face vs online remote session

Age is considered the most significant risk factor for OAB, and understanding of CBT may differ depending on age, as well as the effectiveness of the intervention. We believe that the severity of OAB has a strong influence on the effectiveness of the intervention. Intervention effectiveness may differ depending on whether CBT alone or in combination with oral medication is used. Urinary incontinence is caused by weakness of the pelvic floor muscles, and the intervention effect may differ depending on the presence or absence of urinary incontinence. CBT is a psychotherapy, and treatment effects may differ in participants with anxiety or depression. Regarding the method of

659 intervention, the treatment effect may differ between face-to-face and online. In  
660 addition, there may be different age groups among the participants who prefer  
661 face-to-face versus online. For these reasons, subgroup analyses will be conducted for  
662 age, severity, presence of urinary incontinence, and HADS scores.

663

#### 664 11.3.4 Sensitivity analysis

665 The ITT will be used as the main analysis, and the PPS will be used as the sensitivity  
666 analysis. Furthermore, sensitivity analyses included multiple imputation approach for  
667 imputing missing data will be performed, with missing at random assumptions.

668

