 593 hallucinations/delirium, QT prolongation, ventricular tachycardia

594

595 Beta 3-adrenergic receptor agonist

596 Main side effects: constipation, dry mouth

597 Serious side effects: urinary retention, hypertension

598

599 11. Statistical consideration

600 11.1 Sample size and rationale

601 Assuming a significance level of 5% bilaterally, a power of 80%, a symptom score  
 602 difference between groups (OAB-q) of 10, and a standard deviation of 20, the sample  
 603 size is 128 patients in both groups. Assuming a dropout rate of 15%, the target number  
 604 of participants is 150 in both groups.

605

606 11.2. Analysis participants

607 As an intention-to-treat (ITT) analysis, all participants for whom allocation have been  
 608 initiated will be included in the analysis. Only patients who adhere to this protocol (Per  
 609 Protocol Set: PPS) will also be analyzed as a sensitivity analysis.

610 Definition of PPS: Participants who meet the following 4 criteria

611 (1) Patients have received all intervention treatments.

612 (2) Intervention interval is less than 3 weeks.

613 (3) Patients have not received additional medical treatment for OAB at other hospitals

614 (4) All measurement data are available.

615

616 11.3 Statistical analysis

617 11.3.1 Primary analysis

618 A mixed-effects model with repeated-measures (MMRM) will be used to analyze the  
 619 primary outcome, the HRQoL total score of OAB-q, under the assumption of missing at  
 620 random. Estimates of the least squares mean group difference, 95% confidence interval,  
 621 and p-value will be calculated as the result of group  $\times$  time point estimation with the  
 622 change from baseline to each measurement point as the objective variable, treatment

group, time point, OAB severity, interaction between treatment group and time point as fixed effects, study participants as variable effects, and baseline values as covariates. Week 13 is the assessment point for the primary analysis. A multiple-testing procedure will be used to control for the familywise type I error rate at a two-sided significance level of 0.05. If the primary analysis at week 13 shows statistical significance, testing of other assessment points of the primary outcome is to be performed in a hierarchical manner: week 9 and week 5.

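### Neither sensitivity analysis named in Section 11.3.4 departs from missing at random, so neither can show whether the week-13 result depends on that assumption

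*Protocol*

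**What the plan says.** Protocol Section 11.3.1 applies the MMRM to the "primary outcome, the HRQoL total score of OAB-q, under the assumption of missing at" random, with week 13 as the primary time point.

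Section 11.3.4 then sets out the sensitivity analyses:

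- **Analysis set.** "The ITT will be used as the main analysis, and the PPS will be used as the sensitivity" analysis. One of the four PPS criteria in Section 11.2 is "4) All measurement data are available", so anyone with a missing assessment is excluded.
- **Missing data.** The section adds a "multiple imputation" analysis and fixes its assumption: "imputing missing data will be performed, with missing at random assumptions".

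No delta-adjusted, tipping-point, reference-based or other missing-not-at-random analysis is named anywhere in the protocol.

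Other sections bear on how plausible MAR is:

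- Participants and outcome adjudicators are unmasked (Section 8), and the primary outcome is a self-completed questionnaire (Section 6.2).
- Controls receive CBT only after the study ends (Section 5.4).
- If a participant withdraws consent, data already collected are not used either (Section 15.5).
- Participants who deviate from or stop the intervention stay under scheduled evaluation unless they withdraw consent for it (Sections 9.1 and 9.2).

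**The concern.** A sensitivity analysis for missing data should change the untestable part of the primary analysis, which is what is assumed about the outcomes nobody saw. Here the primary analysis and the imputation make the same assumption. If both use similar variables they estimate the same quantity and should nearly agree, whether or not MAR is true. The PPS changes who is analysed and leaves incomplete cases out. If its result differs from the ITT result, adherence and missingness cannot be told apart.

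MAR is open to doubt in this trial. Participants know their arm and rate themselves, and the arms have different reasons to leave: disappointment with CBT in one, and waiting for it in the other. Section 15.5 makes this worse for anyone who withdraws consent. Their week 5 and week 9 scores are removed, and those are the scores that would have made MAR more credible.

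What is at stake is a statement of robustness in the final report that the planned analyses cannot support.

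**Working it through.** **Inputs from the protocol**

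- Section 11.1: two-sided 5% level, 80% power, difference 10, SD 20, 128 evaluable, 15% dropout, 150 randomised.
- Section 3: 1:1 allocation.
- Section 6.2: minimum clinically important difference (MCID) of 10 points. The score runs from 0 to 100, and higher is better.

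**Reproducing the plan's figures.** A two-sample t-test with standardised difference 10/20 = 0.5 needs 63.77 per arm, rounded to 64, so 128 in total. This matches. For dropout, 128/0.85 = 150.6 and 150 × 0.85 = 127.5, consistent with the stated 150. The sample size is not in question.

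**Assumptions that are not in the protocol**

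- A share m of the CBT arm has no week-13 score. I take m = 15% and show a range.
- Those participants' true scores lie on average δ points below the MAR prediction.
- Missing control scores follow MAR.
- The standard error stays at its planning value.

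**Effect on the estimate.** The CBT-arm mean falls by m × δ, so the adjusted difference is the observed difference minus m × δ. With m = 0.15 and δ = 10, the loss is 0.15 × 10 = 1.5 points, and a difference of 10 becomes 8.5. The MAR imputation sets δ = 0 by construction.

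**Significance boundary.** SE = 20 × √(2/64) = 3.54, and 1.96 × 3.54 = 6.93 points.

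**Tipping shift.** δ* = (observed difference − 6.93)/m.

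- Observed 10: (10 − 6.93)/0.15 = 20.5
- Observed 8: (8 − 6.93)/0.15 = 7.1

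| CBT arm missing at week 13 | δ* if observed 10 | δ* if observed 8 |
|---|---|---|
| 5% | 61.4 | 21.4 |
| 10% | 30.7 | 10.7 |
| 15% | 20.5 | 7.1 |
| 20% | 15.4 | 5.4 |
| 30% | 10.2 | 3.6 |

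At 15% missing, an observed 10 tips only at a shift about equal to the planning SD and twice the MCID. An observed 8 tips at a shift smaller than the MCID.

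**Effect of baseline adjustment.** The MMRM adjusts for the baseline score. If SD 20 is the raw-score SD and the baseline correlation is 0.5 (both assumed), SE = 3.54 × √(1 − 0.25) = 3.06 and the boundary is 1.96 × 3.06 = 6.0. At 15% missing the tipping shifts rise to (10 − 6.0)/0.15 = 26.7 and (8 − 6.0)/0.15 = 13.3.

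**The case against.** The strongest objection is that nothing in Section 11.3.4 is wrong in itself. Imputation under MAR is legitimate, the wording does not rule out further analyses, and tipping-point details usually sit in a SAP, which was not available here. One should not infer that no such analysis will ever be run. What stands is that the protocol is not silent: it chooses the missing-data check and fixes its assumption to be the same as the primary one. That check cannot inform about MAR whatever a SAP adds.

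Four stronger readings are tempting, and the documents do not support them:

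- **MAR gives every dropout the benefit of those who stayed.** The MMRM conditions on observed scores. A woman who records no benefit at week 5 or 9 and then leaves is predicted from her own poor score. The reading fits mainly those with no usable post-baseline score, or whose later course departs from what was observed.
- **15% of the CBT arm will be missing at week 13.** Section 6.2 defines two kinds of dropout, stopping the intervention and stopping evaluation, and Section 11.1 does not say which the 15% covers. Sections 9.1 and 9.2 keep the first kind under evaluation, and Section 18 offers a gift certificate at each assessment. Missingness may be lower.
- **The imputation must reproduce the MMRM.** That holds only if both use the same variables, which is not stated. OABSS, KHQ and HADS, collected at the same visits, could serve as auxiliary variables. The result would still be a MAR analysis.
- **The trial's conclusion is fragile.** At the planned difference of 10 it is not: assuming dropouts keep no benefit still leaves 8.5, above the boundary. An observed 8 under the same assumption gives 8 × 0.85 = 6.8, just below 6.93, and baseline adjustment could reverse even that.

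**Conclusion.** The point holds in limited form. Neither named sensitivity analysis can show whether the week-13 result depends on MAR, and agreement between the MMRM and the MAR imputation is not evidence that it does not. Continued evaluation after stopping the intervention, and conditioning on the week 5 and 9 scores, reduce the concern. They do not remove it, partly because Section 15.5 deletes those scores for participants who withdraw consent.

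The size depends on the result. With 15% of the CBT arm missing, SD 20 and 64 per arm, a clear effect of 10 would survive any shift short of about 20 points, while an effect of 8 could be overturned by about 7. These figures assume no departure from MAR among controls and no gain in precision from baseline adjustment. Whether data will in fact be missing not at random cannot be known from the protocol. The primary MMRM and the sample size are not challenged. This is a cheap improvement and does not call the design into question.

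**What to change.** In Section 11.3.4, keep the MAR imputation if wanted and add one prespecified analysis of the week-13 primary outcome that departs from MAR:

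- **Tipping point.** Impute missing week-13 scores, subtract δ from the imputed CBT-arm values, and raise δ from 0 in fixed steps until two-sided significance at 0.05 is lost. Report that δ beside the 10-point MCID.
- **Reference-based scenario.** Impute missing CBT-arm values from the control arm, as one named scenario.

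State that agreement between the MMRM and the MAR imputation will not be described as robustness to the MAR assumption. Report the number with missing week-13 scores by arm, separating those whose data are removed under Section 15.5.

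The cost is one or two sentences and a few hours of programming, with no change to enrolment, visits, treatment or the primary analysis. The downside is that the sensitivity estimate may be less favourable than the primary one.

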### 669 12. Study Period

#### 670 12.1 Participant enrollment period

671 Two years and 6 months from the date of approval.

#### 672 12.2 Participant follow-up period

673 Four weeks of CBT and 8 weeks of post-treatment follow-up (total 12 weeks).

674

#### 675 12.3 Study duration

676 Three years from the date of approval.

677

### 678 13. Additional invasions and anticipated risks and benefits of the study

679 There will be a time burden associated with the completion of the self-administered  
680 symptom rating scale and the implementation of the CBT program, but no other specific  
681 risks are anticipated. No AEs were observed in the pilot study. The expected benefit is  
682 that the CBT incorporates behavioral therapy, which has originally been shown to be  
683 effective, and may lead to improvement of symptoms of OAB.

684

### 685 14. Availability of compensation for adverse health effects

686 Although not covered by insurance, this treatment incorporates behavioral therapy  
687 recommended in the guidelines for the treatment of OAB and is an intervention within  
688 the scope of insurance coverage. Therefore, we believe that the anticipated health  
689 hazards can also be covered by insurance. For this reason, no compensation for health  
690 damage is provided. In the event of health damage, each individual will be examined  
691 and treated by the insurance.

692

### 693 15. Protection of personal information

#### 694 15.1 Timing and method of anonymization of samples and information

695 All data will be entered within REDCap. After entry, the data will be anonymized with  
696 serial numbers. After anonymization, research participants will be identified by  
697 manipulating the numbers given to them.

698

#### 699 15.2 Methods for managing the correspondence table

700 A new correspondence table will be created and stored at each facility. The  
701 correspondence list will be stored securely in a computer with a password.

702

#### 703 15.3 Items of personal information to be retained or used, security control measures, 704 and points to note

705 Only the items obtained from the questionnaire will be used. Specifically, the following  
706 information will be used: age, height, weight, medical history, childbirth experience,  
707 menopause, last education, marital history, occupational history, treatment for voiding  
708 dysfunction, primary outcome, secondary outcomes, and AEs. As a security measure,  
709 data will be managed in REDCap, access to REDCap will be restricted to researchers,  
710 and all access will be logged in the system.

711

#### 716 15.5 Handling of data after withdrawal of consent

717 Data after withdrawal of consent will not be used. Data obtained before the withdrawal  
718 of consent by the person withdrawing consent will also not be used.

719

### 720 16. Explanation and consent

#### 721 16.1 Rules and regulations to be observed

722 In accordance with the "Declaration of Helsinki of the World Medical Association" and  
723 the "Ethical Guidelines for Life Sciences and Medical Research Involving Human  
724 Participants," we guarantee that the research participants can discontinue this research at  
725 any time if they so desire. When a research participant requests discontinuation of  
726 participation in the research, the use of such data will be discontinued.

727

#### 728 16.2 Written explanation and consent form

729 The attached explanation and consent forms will be used.

730

731 17. Methods for storage and disposal of samples and information

732 17.1 Period of storage of information

733 Registered data will be stored at the Department of Urology, Kyoto University School  
734 of Medicine, and at each institution for 10 years after publication.

735

736 17.2 Method of information storage (measures to prevent leakage, mix-up, theft, loss,  
737 etc.)

738 Data collected at each institution will be stored in a database on REDCap, with each  
739 institution's individual participant identifiers deleted and a new research ID assigned.  
740 Access to REDCap will be restricted to researchers to prevent leakage, mix-up, theft, or  
741 loss. In addition, the system keeps a history of all accesses, which should allow for  
742 contingency measures.

743

744 17.3 Disposal after the retention period, if any

745 After the retention period, if consent is obtained, the correspondence list will be  
746 destroyed and uploaded to the UMIN ICDR in a form that does not identify specific  
747 individuals and stored semi-permanently.

748

749 17.4 When providing and receiving information from other research institutions, create  
750 and maintain records related to the provision of such information

751 We are considering the possibility of providing information to other research periods by  
752 uploading it to the UMIN ICDR. Since the UMIN ICDR can only be used to provide  
753 information to designated researchers, the creation and management of records will be  
754 shared. Conversely, the same will apply to the provision of information.

755

756 18. Cost sharing and honoraria

757 The intervention group will require office visits for intervention (weeks 1, 2, 3, and 4)  
758 and follow-up (weeks 5, 9, and 13); the control group will require office visits for  
759 allocation (week 1) and follow-up (weeks 5, 9, and 13). The cost of the hospital visits  
760 (re-consultation fees only) will be borne by the study participants within the insurance  
761 reimbursement. However, if the participants wish to participate in the online  
762 intervention, the consultation fee at the time of intervention will not be required. As for  
763 the gratuity, both groups will receive a gift certificate worth 1,000 yen at the week 5, 9  
764 and 13 visits after answering each assessment item.

765

766 19. Research funding and conflict of interest

767 This study is funded by a donation (Grant-in-Aid for Urology Research) and  
768 Grant-in-Aid for Young Scientists (20K18964) from the Ministry of Education, Culture,  
769 Sports, Science and Technology of Japan.

770 Conflicts of interest are appropriately reviewed by the Kyoto University Clinical  
771 Research Conflict of Interest Review Committee in accordance with the Kyoto  
772 University Conflict of Interest Policy and the Kyoto University Conflict of Interest  
773 Management Regulations.

774

775 20. Content and method of reporting to the Ethical Review Committee and the head of  
776 the research institution

777 If facts or information that undermine or may undermine the ethical validity or scientific  
778 rationality of the research are obtained, a report on safety information will be made  
779 promptly. If facts or information that undermine or may undermine the appropriateness  
780 of research implementation or the reliability of research results are obtained, a report of  
781 nonconformity will be promptly submitted. Annual reports will be made annually.

782 Reports on discontinuation or termination will be made as appropriate. Conference  
783 presentations and papers of the results will be attached to the electronic submission  
784 system in PDF format. The final publication of the results shall also be reported.

785

786

787 21. Attribution of research results and publication of results

788 The research results obtained in this study belong to Kyoto University. The results will  
789 be published in academic conferences and papers. In addition, the results will be  
790 pre-registered, updated, and registered in the public database of UMIN (accession  
791 number: UMIN000038513).

792

793 22. Measures to be taken regarding the provision of medical care to research  
794 participants after the research is conducted

795 After the research is conducted, efforts will be made to ensure that research participants  
796 receive the best possible treatment using the findings from the research.

797

798 23. Recruitment of participants

799 The recruitment for this study will include the leaflet, information sessions for the  
800 public, information sessions for physicians, introduction of the study on the laboratory's  
801 website, internet advertisement, newspaper advertisement, poster placement, and leaflet  
802 distribution.

803  
